### Statistical Methods for Safety Outcomes

The safety analysis will encompass the severity of adverse events, their causal relationship with the intervention, the incidence rate of adverse events by group, the rate of adverse events leading to dropout, and the incidence rate of serious adverse events. The proportion of participants who dropped out due to treatment failure or adverse events will be reported for each group, along with 95% CI. In addition, the chi-square test or Fisher exact test may be used to compare observed frequencies against expected frequencies. Also, the number of cases assessed as having a high risk of suicide during the study period will be presented by group, and statistical testing may be conducted if necessary.

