**Figure 2 figure2:**
[figure not shown]
Acupoint TF4. Adapted from Qu et al [17], under the Creative Commons Attribution 4.0 International License (CC BY 4.0).

To ensure the rigor and validity of our findings, this study protocol (version 1.4, June 2023) adheres to the SPIRIT (Standard Protocol Items: Recommendations for Interventional Trials) guidelines.

Study Procedure

During the initial screening visit, potential participants will receive a comprehensive explanation of the study’s purpose, procedures, risks, and benefits and will be asked to provide written consent. Those who voluntarily consent and meet the inclusion and exclusion criteria—as determined through demographic information surveys, medical and medication history reviews, vital signs measurements (blood pressure, pulse, and temperature), laboratory tests, pregnancy tests, the Structured Clinical Interview for *DSM-5* (*Diagnostic and Statistical Manual of Mental Disorders* [Fifth Edition]; SCID-5) [18], and the Columbia Suicide Severity Rating Scale (C-SSRS) [19]—may be enrolled in this study. The SCID-5 will be used to diagnose subtypes of anxiety disorders, including social anxiety disorder, panic disorder, agoraphobia, generalized anxiety disorder, and other specified anxiety disorders. Participants who do not meet the diagnostic criteria for an anxiety disorder as per the SCID-5 will be excluded from the study. The C-SSRS will be used to assess the risk of suicide; participants scoring 4 or above, indicating a high risk of suicide, will also be excluded from study selection.

Following registration, participants will be randomly assigned to one of the three groups: the electroacupuncture-vagus nerve stimulation (EA-VNS) group, the electroacupuncture-median nerve stimulation (EA-MNS) group, or the usual care group. Participants in the treatment groups will undergo electroacupuncture sessions twice weekly for a total of 16 sessions over 8 weeks. Conversely, the usual care group will not receive any interventions during this period.

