The evaluation of the treatment group is scheduled to occur at the initial, eighth, and final visits. For the control group, assessments will be conducted in the first, fourth, and eighth weeks. During the initial and final assessments for the treatment group, and the first and eighth weeks for the control group, the following instruments will be administered: Hamilton Anxiety Rating Scale (HAM-A) [20], Beck Anxiety Inventory (BAI) [21], Beck Depression Inventory-II (BDI-II) [22], Patient Health Questionnaire-15 (PHQ-15) [23], World Health Organization Quality of Life Assessment Instrument abbreviated version (WHOQOL-BREF) [24], Leibowitz Social Anxiety Scale-Self Report (LSAS-SR) [25], The Panic Disorder Severity Scale (PDSS) [26], and Penn State Worry Questionnaire (PSWQ) [27]. LSAS-SR will be conducted only for patients with social anxiety disorder, PDSS only for those with panic disorder or agoraphobia, and PSWQ only for those with generalized anxiety disorder. A midpoint evaluation using the HAM-A and BAI will be conducted during the eighth visit for the treatment group or in the fourth week for the control group. The detailed schedules are described in Table 1 and the study flow is presented in Figure 3.

**Table 1 table1:** Timeline of the trial.

Period				Screening (week –1)		Treatment									
						Baseline (week 0)	Midterm						Final (week 8)		
							Weeks 1-4		Week 4		Week 5-8				
Visit						Visit 1^a^	Visit 2-7^b,c^		Visit 8		Visit 9-15		Visit 16		
Consent				✓											
Demographic information				✓											
Medical history				✓		✓	✓		✓		✓		✓		
Physical examination				✓											
Vital signs				✓		✓	✓		✓		✓		✓		
Body weight and height				✓									✓		
Laboratory test^d^				✓											
Pregnancy test^e^				✓											
SCID-5^f^				✓											
C-SSRS^g^				✓									✓		
Inclusion and exclusion criteria				✓											
Randomization						✓									
	Item														
		HAM-A^h^, BAI^i^				✓			✓				✓		
		PHQ-15^j^, BDI-II^k^				✓									
		WHOQOL-BREF^l^				✓							✓		
		PSWQ^m^, PDSS^n^, LSAS-SR^o^				✓							✓		
		EQ^p^, PSS^q^				✓							✓		
Emotional reactivity test						✓							✓		
Check concomitant drugs						✓	✓		✓		✓		✓		
Check adverse effects						✓	✓		✓		✓		✓		
EA-MNS^r^, EA-VNS^s^						✓	✓		✓		✓		✓		
HRV^t^						✓			✓				✓		
Education of visit schedule				✓		✓	✓		✓		✓				

^a^Visit 1 is scheduled to occur within 10 days of screening.

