^b^Visits 2-7 are implemented 4 times within 2 weeks + 2 days from visit 1. Similarly, visits 9- 15 are implemented 4 times within 2 weeks + 2 days after visit 8. Electroacupuncture treatments are typically scheduled twice a week, but once to three visits per week are permitted.

^c^Only the experimental group follows this schedule.

^d^Lab test items are as follows: complete blood cell count (red blood cell, white blood cell, hemoglobin, hematocrit, platelet, erythrocyte sedimentation rate, white blood cell differential count), blood chemistry test (aspartate aminotransferase, alanine aminotransferase, blood urea nitrogen, creatinine, and hemoglobin A_1c_), thyroid function test (triiodothyronine, free thyroxine, and thyroid stimulating hormone), pregnancy test (urine human chorionic gonadotropin, applicable only to fertile women).

^e^A pregnancy test is only performed for fertile women who have had a menstrual period within the last year.

^f^SCID-5: Structured Clinical Interview for DSM-5 (Diagnostic and Statistical Manual of Mental Disorders [Fifth Edition]).

^g^C-SSRS: Columbia Suicide Severity Rating Scale.

^h^HAM-A: Hamilton Anxiety Rating Scale.

^i^BAI: Beck Anxiety Inventory.

^j^PHQ-15: Patient Health Questionnaire-15.

^k^BDI-II: Beck Depression Inventory-II.

^l^WHOQOL-BREF: World Health Organization Quality of Life Assessment Instrument abbreviated version.

^m^PSWQ: Penn State Worry Questionnaire. This has been used for generalized anxiety disorder and other anxiety disorders.

^n^PDSS: Panic Disorder Severity Scale.

^o^LSAS-SR: Leibowitz Social Anxiety Scale-Self Report. This has been for social anxiety disorder.

^p^EQ: Empathy Quotient.

^q^PSS: Perceived Stress Scale.

^r^EA-MNS: electroacupuncture-median nerve stimulation. This will be conducted according to each group.

^s^EA-VNS: electroacupuncture-vagus nerve stimulation. This will be conducted according to each group.

^t^HRV: heart rate variability.

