### Adverse Events

In this clinical trial, adverse events are defined as any harmful or unintended signs, symptoms, or diseases occurring in participants. It should be noted that not all such events necessarily have a causal relationship with the intervention. Serious adverse events include death or life-threatening situations, hospitalization or prolongation of existing hospitalization, permanent or significant disability or impairment, congenital anomalies or defects in a fetus, or other medically significant conditions such as drug dependency or abuse. However, not all adverse events are regarded as serious.

From the start of the intervention, any adverse events will be documented in detail, including the date of onset and resolution, the severity and outcome, the actions taken in relation to the intervention and the causal relationship with the intervention, any other suspected treatments or medications, and whether treatment for the adverse event was administered. During the study period, any serious adverse events must be reported by the research team to the principal investigator within 24 hours. The principal investigator is required to report all serious adverse events to the institutional review board in accordance with clinical trial regulations.

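### Adverse events are asked about at about 15 post-baseline visits in the electroacupuncture arms but only 2 in usual care, so recorded non-serious incidence against usual care leans toward electroacupuncture

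*Protocol article*

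**What the plan says.** All references are to the protocol article.

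- **Planned analysis.** Statistical Methods for Safety Outcomes lists "the incidence rate of adverse events by group" among the safety results and adds that "the chi-square test or Fisher exact test may be used to compare observed frequencies against expected frequencies". Study Design sets the aim as efficacy and safety relative to usual care.
- **When adverse events are asked about.** The row "Check adverse effects" in Table 1 is ticked at Visit 1, Visits 2-7, Visit 8, Visits 9-15 and Visit 16.
- **Who attends.** Study Procedure: "Participants in the treatment groups will undergo electroacupuncture sessions twice weekly for a total of 16 sessions over 8 weeks". For usual care, the same section says: "For the control group, assessments will be conducted in the first, fourth, and eighth weeks". Footnote c of Table 1, printed on Visits 2-7, reads: "Only the experimental group follows this schedule".
- **Visit count.** Footnote b reads: "Visits 2-7 are implemented 4 times within 2 weeks + 2 days from visit 1". It gives the same count of four for Visits 9-15, although the table numbers six visits in the first block and seven in the second.
- **Start of recording.** The Adverse Events section says: "From the start of the intervention, any adverse events will be documented in detail". Safety Variables instead covers every event during the trial, and the Safety Analysis Set is defined from random assignment.

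**The concern.** The number of minor events recorded depends on how often people are asked. Here the arms differ greatly in that respect, and the incidence table puts them side by side. A participant seen twice a week is likely to mention a headache or a bad night. A participant asked once in four weeks may have forgotten it. The same background rate would then give a higher recorded incidence in both electroacupuncture arms.

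Safety against usual care is a stated aim, so readers will compare the columns whether or not a test is run. Part of any excess of non-serious events could come from the frequency of asking. Nothing in the article equalises the enquiry, adjusts for it or limits the comparison.

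**Working it through.** **1. Count the enquiries.** Twice weekly for 8 weeks is 2 × 8 = 16 sessions, which reproduces the article's own figure and matches Visits 1-16. Visit 1 is baseline, so Visits 2-16 give 15 post-baseline enquiries. Controls have weeks 4 and 8 after their first-week baseline, which gives 2. The ratio is 15/2 = 7.5. If footnote b is taken literally, the electroacupuncture count is 4 + 1 + 4 + 1 = 10 and the ratio is 5. Footnote c is marked only on Visits 2-7, so the absence of controls at Visits 9-15 is inferred from the Study Procedure text.

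**2. Fixed recall limit.** Assumptions not in the documents:
- the true rate r per participant-week is the same in all arms;
- electroacupuncture capture is complete;
- controls report only events from the last L days at each of their two assessments;
- controls report nothing spontaneously in between.

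The probability of at least one recorded event is 1 − exp(−r × weeks covered). The weeks covered are 8 for electroacupuncture and 2 × L/7 for controls. For r = 0.05 and L = 7, this gives 1 − exp(−0.40) = 0.330 against 1 − exp(−0.10) = 0.095, a ratio of 3.5.

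| r per week | Electroacupuncture | Control, L = 7 | L = 14 | L = 21 | L = 28 |
|---|---|---|---|---|---|
| 0.03 | 0.213 | 0.058 (ratio 3.7) | 0.113 (1.9) | 0.165 (1.3) | 0.213 (1.0) |
| 0.05 | 0.330 | 0.095 (3.5) | 0.181 (1.8) | 0.259 (1.3) | 0.330 (1.0) |
| 0.10 | 0.551 | 0.181 (3.0) | 0.330 (1.7) | 0.451 (1.2) | 0.551 (1.0) |

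**3. Gradual forgetting.** As a check on the hard cut-off, suppose that the chance of reporting an event halves every h days until the next visit. The share captured over a gap of g days is (1 − exp(−kg))/(kg), with k = ln 2/h. The mean gap is 56/15 = 3.7 days for electroacupuncture and 28 days for controls. The Fisher column is the probability of a false two-sided 5% rejection at 20 v 20, with 0.5 to 2 true events per participant over 8 weeks.

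| Half-life h (days) | Captured, electroacupuncture | Captured, control | Ratio of event counts | False Fisher rejection |
|---|---|---|---|---|
| 7 | 84% | 34% | 2.5 | 18-47% |
| 14 | 91% | 54% | 1.7 | 9-16% |
| 28 | 96% | 72% | 1.3 | 4.5-6% |
| 56 | 98% | 85% | 1.2 | about 3% |

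With equal enquiry the same test rejects in about 2-2.5% of trials. Taking 10 visits instead of 15, the mean gap is 56/10 = 5.6 days. At h = 7 the captured shares are then 77% v 34%, a ratio of 2.3, so the visit-count ambiguity matters little.

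**4. Start of recording.** Table 1 places randomisation, the adverse-event check and the first session all at Visit 1. Counting from the first session or from randomisation therefore opens the window at the same visit.

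**The case against.** Much of the case on the other side stands.

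- **Size.** The article gives no recall limit and requires onset and resolution dates for any event, which points to enquiry about the whole interval. With complete recall there is no bias. A reader might take 1.8-3.5 as the bias in this trial, but that range belongs to an assumed 7- to 14-day cut-off.
- **Start date.** A reader might infer that recording from the start of the intervention leaves controls without a window and adds a second bias. The documents do not support this: Visit 1 holds both randomisation and the first session, and Safety Variables and the Safety Analysis Set definition give controls an anchor. It is a wording inconsistency.
- **Testing.** A reader might infer that a between-arm test of incidence is committed. It is only permitted. The incidence table is planned, however, and carries the imbalance by itself.
- **Separating harm.** It would be too strong to say that the safety data cannot distinguish harm from frequency of asking. Severity and causality are assessed for each event, and serious events and dropouts due to adverse events are reported separately.
- **Inherent imbalance.** An untreated comparator has fewer contacts, the direction overstates harm and does not hide it, and a full protocol that is not shown may describe how controls are asked. Even so, the schedule printed here fixes unequal enquiry and the analysis section takes no account of it.

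**Conclusion.** The point holds in a limited form. On the printed schedule, recorded non-serious incidence against usual care is biased toward electroacupuncture unless controls recall four weeks completely. The direction follows from the 15 v 2 (or 10 v 2) enquiries. The size rests on assumed recall, an assumed event rate and no spontaneous reporting by controls. At 0.05 events per participant-week the apparent risk ratio runs from 1.0 (28 days) through about 1.3 (21 days) to 1.8-3.5 (14 to 7 days). Gradual forgetting gives event ratios of 1.2-2.5. Serious events and events leading to dropout are less affected. EA-MNS against EA-VNS is unaffected, because both follow the same schedule.

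The article's Results section says that data collection ended in November 2024 and that analysis is underway. Enquiry can no longer be equalised, but the safety analysis can still be worded to allow for it.

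**What to change.** In Statistical Methods for Safety Outcomes:

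1. Base any incidence contrast or test against usual care on events with onset, or still ongoing, in the same short fixed window (for example 7 days) before the week 4 and week 8 assessments in all three arms. Add serious events and events leading to dropout over the whole period.
2. Report all session-elicited events as electroacupuncture-only rates, per participant and per session, with no test against controls.
3. State that enquiry frequency differed and that some imbalance remains within the window. At the usual two sessions a week, a 7-day window still holds about two electroacupuncture visits against one control assessment. A 14-day window would hold about four against one, so the window should be short.

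As wording only, reconcile the Adverse Events section with Safety Variables and the Safety Analysis Set by counting from randomisation in all arms. The visit count in footnote b also needs reconciling with the numbered visits. The revision should be dated and described as made after data collection ended.

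**Cost.** The change needs new wording and one extra table from onset and resolution dates already required. Fewer events enter the comparison with usual care: two 7-day windows cover 2 of 8 weeks. At 0.05 events per week and counting onsets only, about 20 × 0.095 = 1.9 participants per arm would have one. The full electroacupuncture listing is kept.

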### Statistical Methods to Handle Missing Data

When using the MMRM for variable analysis, no separate imputation for missing values will be conducted. Conversely, in cases where ANCOVA is used, missing values will be imputed using the Multiple Imputation method.

### Statistical Analysis of Demographic and Baseline Characteristics

In this study, descriptive statistics for demographic and pretreatment characteristics will be presented for each group. Continuous variables will be analyzed using either ANOVA or the Kruskal-Wallis test, depending on the data distribution. Categorical variables will be analyzed using the chi-square test or Fisher exact test; Fisher exact test will be applied when more than 25% of cells in a contingency table have an expected frequency of less than 5. If necessary, significant differences in baseline characteristics between groups will be adjusted for by incorporating these characteristics as covariates in the efficacy variable analysis.

### Study Protocol Modifications

Any modifications to the study protocol require prior approval from the institutional review board. This clinical trial will adhere to the approved protocol unless deviations are necessary to eliminate immediate risks to participants.

### Adverse Events

In this clinical trial, adverse events are defined as any harmful or unintended signs, symptoms, or diseases occurring in participants. It should be noted that not all such events necessarily have a causal relationship with the intervention. Serious adverse events include death or life-threatening situations, hospitalization or prolongation of existing hospitalization, permanent or significant disability or impairment, congenital anomalies or defects in a fetus, or other medically significant conditions such as drug dependency or abuse. However, not all adverse events are regarded as serious.

From the start of the intervention, any adverse events will be documented in detail, including the date of onset and resolution, the severity and outcome, the actions taken in relation to the intervention and the causal relationship with the intervention, any other suspected treatments or medications, and whether treatment for the adverse event was administered. During the study period, any serious adverse events must be reported by the research team to the principal investigator within 24 hours. The principal investigator is required to report all serious adverse events to the institutional review board in accordance with clinical trial regulations.

### Dropout

In this study, dropout refers to the termination of participation before completing all phases of the study. Researchers can stop treatment and observation and withdraw the participant, or participants can voluntarily withdraw at any time. A participant may be considered dropped out under the following circumstances:

If it is discovered after screening that the participant does not meet the inclusion or exclusion criteria.If a systemic disease not identified during pretreatment examinations, is discovered.If the participant experiences a serious adverse event and the researcher determines that continued participation is inappropriate.If an adverse event is severe enough that the researcher deems continued participation to be inappropriate.If symptoms worsen and the researcher determines that other treatment is necessary.If the participant withdraws consent or requests to stop participation.If the participant does not visit or cannot be followed up.If the researcher determines that continuation of the clinical trial is inappropriate for any other reason.

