## Methods

Study Design

This study is designed as a randomized, 3-arm assessor-blinded, parallel-group clinical trial, which will be conducted at the Daejeon Korean Medicine Hospital of Daejeon University, Republic of Korea. It aims to evaluate the efficacy and safety of 2 distinct electroacupuncture interventions in the treatment of anxiety disorders, in comparison to usual care. The interventions specifically target to stimulate the median nerve via acupoint PC6 and the vagus nerve via acupoint TF4 (Figures 1 and 2) [16,17]. The control group, constituting usual care, will not receive any treatment.

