#### Prohibited Drugs

During the trial period, the administration of drugs that may influence anxiety symptoms is prohibited, including systemic steroids, antipsychotics, antidepressants, benzodiazepines, and sleeping pills. However, if antidepressants, benzodiazepines, and sleeping pills have been administered at a stable dose for at least 2 weeks before screening, their continuous use may be permitted.

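### Worsening that needs other treatment can end observation, so week-8 HAM-A can be missing because of the outcome; the MMRM repairs this only if the worsening was recorded at week 4

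*Protocol article*

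**What the plan says.** The primary outcome is HAM-A change from baseline to week 8, each electroacupuncture arm against usual care (Efficacy Variables). HAM-A is taken at baseline, at the midpoint (visit 8 or week 4) and at the end (Study Procedure, Table 1).

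Under Dropout, "dropout refers to the termination of participation before completing all phases of the study". The same section says "Researchers can stop treatment and observation and withdraw the participant, or participants can voluntarily withdraw at any time". The list of circumstances is introduced by "A participant may be considered dropped out under the following circumstances" and includes "If symptoms worsen and the researcher determines that other treatment is necessary".

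Under Prohibited Drugs, "During the trial period, the administration of drugs that may influence anxiety symptoms is prohibited", with an allowance for some drugs already taken at a stable dose. Of the comparator, Study Design says "The control group, constituting usual care, will not receive any treatment".

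The Full Analysis Set (FAS) is said to follow the intent-to-treat principle but requires at least one post-baseline primary outcome. The Per Protocol Set removes anyone who meets a dropout criterion (Definition of the Analysis Set). The primary model is an MMRM, and "When using the MMRM for variable analysis, no separate imputation for missing values will be conducted". Multiple imputation is planned only for the ANCOVA, which is run only if baselines differ significantly.

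**The concern.** One listed reason for leaving the trial is a bad course on the symptom that the primary endpoint measures. Dropout ends participation, and no section of the article schedules a HAM-A at withdrawal or afterwards. A missing week-8 score may therefore be missing because it would have been high.

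Unequal loss is plausible. The comparator receives no study treatment for 8 weeks, participants know their arm, and withdrawal rests on a researcher's judgement that the Dropout section does not require to be blinded. If the worst controls are lost, the control mean at week 8 looks better than it was and both primary contrasts shrink. If worsening, or the readiness to withdraw, is greater in an electroacupuncture arm, the error runs the other way.

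An MMRM without imputation is valid when the missing value is predictable from what was observed (missing at random). Week 4 is the only post-baseline observation before the endpoint, so everything depends on whether the worsening shows there.

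**Working it through.** **What the article gives.** Enrolled 60, completed the intervention 51, so 60 - 51 = 9 and 9/60 = 15% did not complete (Results). The Sample Size section moves from 15 to 20 per group; 1 - 15/20 = 25% is the implied allowance for loss. That allowance protects numbers, not against outcome-related loss. No SD, effect size, correlation or dropout rate is stated, so every input below is an assumption.

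**Three paths by timing**

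1. Worsening recorded at week 4, then dropout: the model has the score that drove the loss.
2. Worsening after week 4: the participant stays in the FAS, but the worsening is never recorded.
3. Dropout before week 4: no post-baseline HAM-A, so the participant leaves the FAS.

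**Size in the contrast.** Large-sample simulation, 200,000 per arm. Assumed: SD 7; baseline mean 22; control change -1; correlation of adjacent visits 0.5 or 0.7; worsening defined as a rise of at least 5 points since the previous assessment; dropout after worsening with probability 0.5 or 1, same rule in both arms. The target effect of -5 was realised as -4.97 (correlation 0.5) and -5.02 (correlation 0.7). Attenuation = estimate minus realised effect. Unstructured MMRM:

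| Path | Dropout probability | Correlation 0.5: estimate (attenuation) | Correlation 0.7: estimate (attenuation) |
|---|---|---|---|
| 1. Recorded at week 4 | 1 | -4.97 (0.00) | -5.01 (0.01) |
| 2. After week 4 | 0.5 | -4.69 (0.28) | -4.75 (0.27) |
| 2. After week 4 | 1 | -4.22 (0.75) | -4.37 (0.65) |
| 3. Before week 4 | 0.5 | -4.76 (0.21) | -4.79 (0.23) |
| 3. Before week 4 | 1 | -4.41 (0.56) | -4.51 (0.51) |

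With probability 1, about 15 to 22% of controls and 7 to 13% of the electroacupuncture arm are lost. As a share of the effect, paths 2 and 3 cost from 0.51/5.02 = 10% to 0.75/4.97 = 15% at probability 1, and from 0.21/4.97 = 4% to 0.28/4.97 = 6% at probability 0.5. A random-intercept model, which is how the stated participant random factor might be fitted, gives -4.90 and -4.88 on path 1 (attenuation 0.07 and 0.14).

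With an assumed true effect of -3, attenuation on paths 2 and 3 is about 0.1 to 0.5 points. With a true effect of 0 and the same rule in both arms, bias is about 0 on all three paths.

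**Upper range in one arm.** Take 20 controls, SD of change 7, week-4/week-8 correlation 0.5 or 0.7, and delete exactly the k worst week-8 values after week 4. Estimate the week-8 mean by regressing week 8 on week 4 in those remaining and averaging the prediction over all 20 (20,000 replicates). Shift in the control mean at correlation 0.5 / 0.7:

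- k = 2: -1.03 / -0.74
- k = 3: -1.48 / -1.09
- k = 4: -1.93 / -1.46

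That is 0.74/7 = 0.1 to 1.93/7 = 0.3 SD. If the lost controls are instead drawn at random from the worst 7 of 20, the shift is 0.4 to 0.6 points for 2 lost and 0.7 to 0.9 for 3.

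**Hand check.** If k of 20 controls are lost and each is D points worse than the model predicts, the contrast shifts by (k/20) x D. For k = 3: 0.15 x 5 = 0.75 points, or 0.15 x 10 = 1.5 points.

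**The case against.** The wording is permissive. A participant may be considered dropped out and researchers can stop observation; neither is automatic. A reader might infer that everyone who worsens is removed and that the drug prohibition leaves no way to stay. The article does not support that: the prohibition covers drugs, whereas the other treatment in the Dropout list is not confined to drugs. This stands, but discretion does not remove the problem. It leaves open whose endpoint is observed, and no text secures the assessment.

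A reader might also infer that controls are wholly untreated and were lost in excess. Stable antidepressants, benzodiazepines and sleeping pills may be continued, and the text gives neither dropout reasons nor a split by arm. (Figure 4 could not be read for this review and may show one.) The 9 non-completers cover all causes and average 3 per arm; nothing in the text shows that any left because of worsening. Excess control loss is an inference.

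The 0.7 to 1.9 points come from a near-worst case: exactly the highest scorers, all after week 4, with no offsetting loss in the other arm. That is correct, and the figure should be read only as an upper range.

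Finally, sensitivity analyses and post-withdrawal procedures are often left to a full protocol or analysis plan, and neither is shown. Their absence from an article is not the point here. The point is that the stated dropout circumstance, FAS condition and missing-data rule together can make the endpoint missing because of the outcome. Reporting of dropouts for treatment failure or adverse events by group is already planned (Statistical Methods for Safety Outcomes), which covers part of the remedy.

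**Conclusion.** The point holds conditionally. The stated rules allow week-8 HAM-A to be lost because a participant did badly. The planned MMRM largely repairs this when week 4 captured the worsening (0 to about 0.1 points), but not when the worsening came later or the participant left before week 4. In those cases the electroacupuncture contrast is attenuated by about 0.2 to 0.8 HAM-A points for an assumed true effect of -5 and SD 7, with 0.7 to 1.9 points as the upper range. Removing early dropouts from the FAS also sits badly with its stated intent-to-treat principle.

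A reader might conclude that the primary contrast is biased outright, or biased in favour of electroacupuncture. The article supports neither. Bias is near zero if there is no true effect and loss follows the same rule in every arm, and in the most plausible pattern it runs against electroacupuncture. It could favour an electroacupuncture arm if worsening or withdrawal decisions were commoner there, which the text does not allow one to judge.

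**What to change.** For any further version of the design: separate stopping the intervention from stopping observation. Keep the already scheduled week-4 and week-8 HAM-A for every randomised participant unless consent to follow-up is withdrawn, and use those scores in the primary analysis, in line with the stated intent-to-treat principle. This costs one sentence and at most two assessments that are already scheduled, for a few participants. The downside is that the estimate then includes the effect of any later treatment, which should be said openly.

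For this trial, the last participant completed the intervention and data collection ended on November 22, 2024, so follow-up can no longer be changed. What can still be done while the analysis is under way:

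- report all dropout reasons and their timing (before or after week 4) by arm, extending the reporting already planned;
- run a sensitivity analysis that includes all randomised participants with a baseline HAM-A;
- add delta-adjusted or reference-based multiple imputation that treats loss for worsening as unfavourable, over a range of deltas fixed before the comparison is seen.

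The cost is one extra table and one or two additional model runs. No change to clinical care, withdrawal decisions or permitted treatment is proposed.
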